### Sampling and randomization

Given the likelihood of information sharing between the students at the same school, the intervention and control groups will be selected from separate schools. A two-stage cluster sampling design will be used to selected study samples. At the first stage, twelve schools will be randomly selected from a list of eligible schools (girls-specific schools and not involved in similar educational intervention) in Qazvin city using a computer-generated random number. The list of schools will be provided by the department for Education in Qazvin. At the second stage, one class will be randomly selected from each school through a simple random method. Ten eligible individuals will be selected using random sampling method. Assigning of schools to the control and intervention groups will be done via random sampling method. Therefore, six schools will be assigned to the intervention, and six schools will be assigned to the control group.

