### Sample size estimation

The estimation of the sample size is based on the study of Wong et al. considering the mean menstrual distress score for intervention group 23.96 ± 4.79 and 26.61 ± 5.1 in the control group [32], alpha = 0.05, and *β* = 0.2; the estimated sample size in each group will be 51 individuals in each group. Peng et al. suggested adding a 20% attrition rate for youth, school-based studies [33], so the estimated sample size for the current study will be 60 individuals for each group. As we have two groups, the total sample will be 120 female students.

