### Procedure

After obtaining the necessary permission to conduct the study, the researcher will attend the selected schools to identify eligible subjects and invite them to participate. The researchers will provide necessary explanations about the purpose of the research and ensure that data remains confidential. Informed consent will be obtained from eligible subjects. It will be explained that participants can withdraw from the research whenever they chose to. For two consecutive months prior to the intervention, an initial assessment of the severity of dysmenorrhea pain and menstrual distress will be performed in the groups. Questionnaires will be completed by the groups within 3 months after the intervention. Data will be collected using paper file storage. No intervention in the control group will be performed, but the educational content after the end of the study will be made available to the control group participants. If needed, the participants in both groups will be able to contact the researcher at any time. A small gift (a set of six colored pens) will be provided to participants to thank them for their participation. Figure 2 shows the timing of outcome measurement and intervention based on the SPIRIT table.

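### Twelve schools are split 6 v 6 by a random draw with no balancing named, leaving a material (about 14 to 29%) but not likely chance of a sizeable baseline gap in distress

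*Protocol article*

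**What the plan says.** Under Sampling and randomization, the protocol article selects 12 schools, then one class per school, and then: "Ten eligible individuals will be selected using random sampling method". On allocation it says "Assigning of schools to the control and intervention groups will be done via random sampling method", with the result that "six schools will be assigned to the intervention, and six schools will be assigned to the control group". The 6:6 count is the only restriction named.

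Under Procedure it says: "For two consecutive months prior to the intervention, an initial assessment of the severity of dysmenorrhea pain and menstrual distress will be performed". The Abstract gives one month before the intervention instead of two. Neither place says whether this assessment comes before or after schools are assigned. Both speak of the groups being assessed, which would fit assessment after assignment.

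Pain on the VAS is screened over two months to establish eligibility (Study design and participants). Data analysis method plans a three-level mixed model with girls nested in schools, and neither names nor rules out adjustment for baseline.

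**The concern.** Only 12 units are randomised. With six schools per arm, a plain draw does not reliably balance anything, including the outcome itself. Schools may differ in mean distress, and a mean of ten girls carries sampling noise even if they do not.

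If the arms start apart by a good part of the planned effect, an unadjusted follow-up comparison inherits that gap, which can enlarge or mask the intervention effect in this one trial. It also leaves a baseline table that readers will question. The plan already collects the measurement that could prevent this, but gives it no stated part in the allocation.

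**Working it through.** **Inputs from the article.** The Sample size estimation section assumes "mean menstrual distress score for intervention group 23.96 ± 4.79 and 26.61 ± 5.1 in the control group". The difference is 26.61 − 23.96 = 2.65 points. The combined SD is √((4.79² + 5.1²)/2) = 4.95. There are 12 schools, 6 v 6, with 10 girls each, so 60 per arm.

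**Assumptions.** The article gives no ICC, so 0 to 0.10 is used. The baseline SD is taken as equal to the planning SD. Baseline is first treated as a single month.

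**The plan's own figure.** The article states no figure for baseline imbalance. The related figure is the sample size of 51 per group. The usual two-sided formula gives 2 × (4.95 × 2.80/2.65)² ≈ 54.7, so 55, not 51. Adding 20% attrition to 51 gives 51/0.8 = 63.75 (64) or 51 × 1.2 = 61.2 (62), not 60. These are separate matters. The gap calculation below uses only the SDs, the effect and the 6 × 10 layout.

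**Baseline gap under a plain draw.** SD of the gap = 4.95 × √(2 × (1 + 9 × ICC)/60). The tail probabilities are normal, two-sided. Half the planned effect is 1.325 points.

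| ICC | SD of gap (points) | P(gap > 1.325) | P(gap > 2.65) |
|---|---|---|---|
| 0 | 0.90 | 14% | 0.3% |
| 0.02 | 0.98 | 18% | 0.7% |
| 0.05 | 1.09 | 22% | 1.5% |
| 0.10 | 1.25 | 29% | 3.3% |

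Simulating 4,000 trials per ICC over all splits agrees with these to about a percentage point. Averaging two baseline months lowers the risk somewhat. At ICC 0.05, with an assumed month-to-month correlation of 0.5 to 0.7, P(gap > 1.325) is 18 to 20%.

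**Baseline gap under a constrained draw.** There are 12!/(6! × 6!) = 924 splits, and a quarter of them is 231. Drawing at random from the 231 with the smallest gap in school mean distress gives a simulated gap SD of about 0.18 to 0.25 points and P(gap > 1.325) of about 0, for ICC 0 to 0.10.

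**Precision of the effect at ICC 0.05.** Assume baseline/follow-up correlations of 0.6 (girls) and 0.8 (schools). In units of the individual variance:

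- Variance of a school mean: V = 0.05 + 0.95/10 = 0.145.
- Covariance of baseline and follow-up school means: C = 0.8 × 0.05 + 0.6 × 0.095 = 0.097.
- Plain draw, unadjusted: 4.95 × √(0.145 × 2/6) = 1.09.
- Baseline fully used: residual variance V − C²/V = 0.145 − 0.097²/0.145 = 0.0801, so 4.95 × √(0.0801 × 2/6) = 0.81.
- Constrained draw, unadjusted: the remaining gap (SD about 0.22) carries over with slope C/V = 0.67, so √(0.81² + (0.67 × 0.22)²) ≈ 0.82.

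In simulation, with each girl's own baseline in the model, the SD is 0.81 under a plain draw and 0.81 under a constrained draw. Over ICC 0 to 0.10 the extra gain from constraining is about 0 to 5% with the girl's own baseline in the model, and about 4 to 10% with the school mean instead.

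**The case against.** The case against is substantial.

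- **A plain draw is valid.** The estimate is unbiased over repeated draws, and chance imbalance is part of the standard error as long as clustering is modelled, which the plan does. This stands: nothing here is an error or contradiction.
- **A reader might infer that a large gap is likely.** The figures do not support that. A gap above half the planned effect stays well under 50% throughout the range, and one as large as the full effect has a chance of only 0.3 to 3.3%.
- **A reader might credit constrained allocation with the whole fall in SD, from 1.09 to about 0.82.** That compares it with an unadjusted analysis, which the article does not specify. Ordinary baseline adjustment after a plain draw gets to about 0.81, so the further gain is small.
- **A reader might assume baseline distress is already in hand when schools are assigned.** The article does not state the order, and its wording fits assessment afterwards. The gap is therefore avoidable through baseline distress only if the sequence is fixed.
- **The article is condensed.** Balancing detail may be in the full protocol. That cannot be excluded, but the article does state an allocation method, and that method includes no balancing.

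What remains is that a risk of one in seven, even at ICC 0, can be almost removed with data the trial collects anyway. Adjustment corrects the estimate but does not make the arms alike at baseline.

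**Conclusion.** The point holds as an inexpensive improvement to the design, not as a flaw that invalidates the trial. Under the allocation as described, the chance of a baseline gap above 1.325 points is about 14 to 29% for an assumed ICC of 0 to 0.10. This is imprecision, not bias. Constraining the draw on school mean baseline distress brings that chance to about zero.

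Most of the precision comes from putting baseline distress in the model. Constrained allocation adds visible balance and about 0 to 10% more. The gap figures rest on the planning SDs and the assumed ICC. The precision figures also rest on the assumed correlations of 0.6 and 0.8.

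**What to change.** 1. In Sampling and randomization and in Procedure, state that baseline distress is completed in all 12 schools before any school is assigned. Reconcile the one-month and two-month descriptions of baseline, so that the balancing variable is defined.
2. Replace the plain draw: list the 924 possible 6 v 6 splits, keep the 231 with the smallest arm difference in school mean baseline distress, and pick one with a computer-generated random number.
3. In Data analysis method, enter baseline distress in the mixed model. This is worth doing even if the allocation stays as it is.

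**Cost.** A short script and a few sentences, with no extra participants or visits. The real cost is timing: no school can be assigned until the last one has returned its baseline, possibly over two menstrual months, and this has to fit the school year. A side benefit is that girls report baseline distress before anyone knows their school's arm.

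**If waiting is not feasible,** balance on the two-month VAS screening scores, provided screening is complete in all schools before assignment. The gain on distress is smaller. With perfect balance on pain, the distress gap SD at ICC 0.05 would be 1.09 × √(1 − ρ²), where ρ is the correlation between school mean pain and school mean distress. The article does not give ρ; assumed values of 0.3 to 0.7 leave about 1.04 to 0.78 points.

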### Intervention

#### Intervention sessions

The sessions will be between 60 and 90 min apiece, and they will run for three consecutive weeks (one session per week). They will be held in groups consisting of 8–10 people [34]. In general, 5 intervention groups will be formed, and 15 educational sessions will be held at the school within 2 months of the sessions. If needed, individual counseling sessions on menstrual distress and common problems for adolescents will also be held.

#### Intervention details

The design of the intervention will be based on the Leventhal self-regulation model [30]. This model seeks to improve the perception of disease by increasing adolescents’ awareness of their menstruation distress, as well as the control of their emotional responses and coping behavior. For this purpose, hypotheses about the self-regulation model will be used to design the training program. A self-regulated paradigm is a conscious personal management system that involves the process of guiding one’s thoughts, behaviors, and emotions to achieve goals. Therefore, the educational material used for adolescent girls will be designed to be performed in three sessions:

The first session will be based on five dimensions of illness perception [35]. This stage is broken into four steps. The first step involves assessing the adolescent’s perception of the nature of menstrual distress. This assessment includes psychological symptoms related to menstrual distress (e.g., anxiety and depression) and physical symptoms (e.g., fatigue, pain, and weakness). It also examines the beliefs of adolescents about the prevalence of menstrual distress and its complications (e.g., beliefs related to the identity of the disease). The second step will involve assessing the girls’ perceptions about the cause of the menstrual distress and their beliefs about menstrual distress, in order to eliminate their untrue beliefs about the causes of this disease. Then, the duration of the illness and the adolescent’s perception of the duration of the illness will be examined (i.e., the timeline). The third step will be concerned with any distress menstruation has on the adolescent’s life (i.e., the consequences). During the last step, the researchers will examine the adolescent’s perception of the efficacy of existing treatments, in order to control and improve the severity of menstrual pain and relieve symptoms of menstrual distress (e.g., ideas about treatment and improvement). This session will include techniques for self-control, verbal encouragement, feedback, behavioral assessment, and ways to successfully control their illness experiences.

After reviewing the first session, the second session will begin. The adolescents will be asked to talk about their feelings and ambiguities about menstrual distress, and their beliefs and knowledge challenged by the researcher. The researchers will provide information to participants relating to how they could change their misperceptions about the disease. They will be asked if they had any questions about the previous session. In the last 30 min of each session, stress and relaxation strategies will be taught, and the adolescents will be asked to practice these techniques.

The third session will involve an evaluation and closure of the sessions. Beforehand, the adolescents will be notified that this session would be the last one. After they arrive, the content of the previous sessions will be reviewed. Then, they will be asked about the impact of new training and experiences on their lives. Problems and obstacles for each adolescent will be explored. Exercises from the previous sessions will be repeated, and their questions answered. Different methods will be used to increase the effectiveness of the training program.

To ensure adolescents are provided sufficient information to relate to the cognitive and psychological dimensions, a booklet will be used, in addition to face-to-face instructional education. The booklet will aim to improve illness perceptions by providing simple illustrations with explanations. The educational content of this booklet will identify and define menstrual distress, provide a brief explanation of misconceptions about the menstrual cycle, and offer activities authorized and unauthorized during the course and instructions about personal hygiene, physical activity, exercise, nutrition, stress-control techniques, and relaxation. The qualitative content of the booklet will be reviewed by ten faculty members. At the end of the three sessions, this booklet will be given to the intervention group. In addition, if participants had any further questions about the study or illness, the researcher’s contact information will be provided to the adolescents.

### Data collection tools

The following four tools will be used to collect data in the present study:
*Demographic and menstrual questionnaire*: This tool will collect data about demographics related to menstrual problems, including age, age of menarche, education level, field of study, marital status, characteristics of the menstrual cycle (e.g., menstrual period and duration of bleeding), pain medication history, drug addiction, height, weight, and body mass index. It will also collect data about the adolescents’ histories of dysmenorrhea or menstrual distress (e.g., in the mother or sister of the adolescent), secondary dysmenorrhea, underlying diseases, and vaginal sex. This questionnaire will be developed based on the aims of the study, and its validity will be evaluated using the content-validity method by the faculty members of midwifery at Qazvin University of Medical Sciences.*Visual analog scale (VAS*): This valid, reliable tool will be used to assess the severity of dysmenorrhea [36]. The tool is a 100-mm ruler, with zero at one end (which indicates complete pain relief) and ten on the other end (which indicated the most severe pain imaginable). Participants will mark the severity of pain on the ruler. This scale is commonly used in pain assessment, due to its ease of use [37].*Moos Menstrual Distress Questionnaire*: This tool was designed by Radolf Moos [38] to investigate the impact of menstrual distress on one’s daily activities. Its internal correlation is reported to be 83% for pain and 94% for autonomic activity. It consists of 47 questions, which are divided into 8 subgroups. It measures the patient’s general complaints about various types of symptoms during menstruation. Participants will be asked to report symptoms experienced during menstruation, according to the Likert scoring system. A score of 1 for a condition will indicate no experience of any symptom, and 4 will suggest the most severe experience (i.e., almost debilitating). The short form of this questionnaire consisted of 16 to 19 questions. It was widely used to examine physical and psychological symptoms during the premenstrual, intra-menstrual, and intermenstrual phases in various contexts [22]. The validity and reliability of the Farsi version of this questionnaire were evaluated by Qorbanalipour et al. [39]. Therefore, it can be used in various studies for therapeutic purposes in the future.*Illness Perceptions Questionnaire*: The IPQ was first developed by Weinman et al., based on the Leventhal model [40]. Its brief, 9-item, version will be used to assess emotional and cognitive perceptions about the disease which was modified to menstrual distress in this study. The first five questions examine the cognitive embodiment of the disease, including outcome, duration, individual control, treatment control, and nature. Two of the questions relate to affective visualization, including anxiety and emotional response. Scores range from 0 to 10, with higher scores indicating more severe misperceptions about the disease. The validity and reliability of the Farsi version of this questionnaire was confirmed by Bazazian and Beheshti.

### Primary outcome

The primary outcome is the perceived menstrual distress of adolescent girls.

### Secondary outcomes

The secondary outcomes are the illness perceptions and severity of dysmenorrhea pain.

### Procedure

After obtaining the necessary permission to conduct the study, the researcher will attend the selected schools to identify eligible subjects and invite them to participate. The researchers will provide necessary explanations about the purpose of the research and ensure that data remains confidential. Informed consent will be obtained from eligible subjects. It will be explained that participants can withdraw from the research whenever they chose to. For two consecutive months prior to the intervention, an initial assessment of the severity of dysmenorrhea pain and menstrual distress will be performed in the groups. Questionnaires will be completed by the groups within 3 months after the intervention. Data will be collected using paper file storage. No intervention in the control group will be performed, but the educational content after the end of the study will be made available to the control group participants. If needed, the participants in both groups will be able to contact the researcher at any time. A small gift (a set of six colored pens) will be provided to participants to thank them for their participation. Figure 2 shows the timing of outcome measurement and intervention based on the SPIRIT table.

**Fig. 2 Fig2:**
[figure not shown]
SPIRIT schedule of enrolment, interventions, and follow-up assessments

### Data analysis method

Collected data will be analyzed on an intention-to-treat basis using MLwin 2.27 [41]. ICC will be calculated within groups and a three-level mixed model will be used with adolescents girls nested in schools. The significance level will be *p* < 0.05. Finally, power of study will be calculated too.

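### With 12 randomised schools the arm effect has 10 degrees of freedom, and the plan sets a 5% level without a small-sample test that would hold it

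*Protocol article*

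**What the plan says.** All references are to the protocol article.

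- **Sampling and randomization** makes the school the randomised unit: "six schools will be assigned to the intervention, and six schools will be assigned to the control group". Ten eligible girls are drawn from each school.
- **Data analysis method** names the analysis population and package, "Collected data will be analyzed on an intention-to-treat basis using MLwin 2.27", then the model, "ICC will be calculated within groups and a three-level mixed model will be used with adolescents girls nested in schools", and then the threshold, "The significance level will be *p* < 0.05".
- **Not stated:** the estimator (maximum or restricted maximum likelihood), the reference distribution for the arm coefficient, its degrees of freedom, or an expected ICC. The ICC is to be calculated from the trial data.
- **Sample size estimation** uses "alpha = 0.05, and *β* = 0.2" with a "mean menstrual distress score for intervention group 23.96 ± 4.79 and 26.61 ± 5.1 in the control group".

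**The concern.** Arm is a school-level factor, so information about its standard error comes from the variation among the 12 schools. Two things can go wrong with so few. Maximum likelihood divides the between-school sum of squares by 12 instead of 10, which makes the standard error too small. A normal reference then uses the critical value 1.960 where t on 10 df needs 2.228. Unless the ICC is very low, either one makes the confidence interval too narrow and rejects a true null more often than the stated 5%.

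The plan specifies its analysis down to the software version and the significance level, but not the element that decides whether that level is met. At stake is the primary comparison, menstrual distress between arms. A p-value a little below 0.05 could come from the choice of reference distribution, and if that choice is left open it can be made after the data are seen.

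**Working it through.** **Inputs from the article:** k = 12 schools, 6 per arm; m = 10 girls per school (about 8 after 20% attrition); level 0.05; means 23.96 and 26.61, SDs 4.79 and 5.1.

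**Assumptions:** two-sided test; equal school sizes; one averaged outcome per girl; ICC from 0 to 0.20, because the article gives none. Repeated monthly measures add no school-level degrees of freedom to the average arm effect.

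The 0.05 level is set by the plan, not derived, so there is no figure to reproduce for the test itself.

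**Step 1: degrees of freedom and critical value.** 12 − 2 = 10. The two-sided 5% point of t on 10 df is 2.228, against 1.960 for the normal. The ratio is 2.228 / 1.960 = 1.137, so the correct interval is about 14% wider for the same standard error.

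**Step 2: ceilings under a normal reference.** When the estimated school variance stays above zero:
- REML: estimate / SE follows t on 10 df, so the type I error is P(|t10| > 1.960) = 7.8%.
- ML: the SE is too small by √(10/12) = 0.913, so it is P(|t10| > 1.960 × 0.913) = P(|t10| > 1.789) = 10.4%.

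**Step 3: dependence on the ICC.** Take total variance 1 and λ = (1 − ICC) + m × ICC. The between-school sum of squares is λ times chi-square on 10 df. The within-school sum is (1 − ICC) times chi-square on 12 × 9 = 108 df. The arm difference has variance 4λ/(km). λ is estimated by the between-school sum divided by 12 (ML) or 10 (REML). Where the school variance would be negative it is set to zero and the two sums are pooled. Simulation under no effect, m = 10:

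| ICC | ML, normal | REML, normal | REML, t(10) | School means, t(10) |
|---|---|---|---|---|
| 0 | 4.8% | 4.1% | 2.1% | 5.0% |
| 0.02 | 6.2% | 5.2% | 2.9% | 5.0% |
| 0.05 | 7.8% | 6.3% | 3.7% | 5.0% |
| 0.10 | 9.3% | 7.3% | 4.5% | 5.0% |
| 0.20 | 10.2% | 7.7% | 4.9% | 5.0% |

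With 8 girls per school the picture is the same: at ICC 0.05, about 7.4% (ML) and 6.1% (REML) with a normal reference.

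**Step 4: price in power.** Difference 26.61 − 23.96 = 2.65; pooled SD √((4.79² + 5.1²)/2) = 4.947. With 60 per arm and an assumed ICC of 0.05, the design effect is 1 + 9 × 0.05 = 1.45. The SE is 4.947 × √(2/60 × 1.45) = 1.088, and 2.65 / 1.088 = 2.436.
- Normal reference: P(Z > 1.960 − 2.436) = 68%.
- t on 10 df (non-central t, non-centrality 2.436): 59%.

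The loss is about 9 points. The normal figure is nominal: it treats the SE as known.

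**The case against.** The strongest case against is that the article contains no wrong statement here. It names a package and a model, not an estimator or a reference distribution, and a condensed article may leave those to a fuller protocol or analysis plan that is not shown. The article also commits to modelling the school clustering, which is the main safeguard.

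A reader might infer from the package name that the trial will use large-sample inference, and that its false-positive rate is therefore well above 5%. The documents do not support either step. Naming the software fixes neither maximum likelihood nor a normal test. The size of any excess depends on an ICC that is not given: a normal reference falls slightly below 5% at ICC 0 and, with REML, is close to nominal at ICC 0.02. The point has to stay conditional.

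Two further objections stand in part. First, REML with t on 10 df is not exact: at ICC 0.02 it gives 2.9%, further from 5% than either normal-reference test in the table. Second, the calculation uses one mean per girl in a balanced two-level layout, whereas the plan has three levels and repeated assessments, and the article does not state which contrast over time is primary. The percentages apply to an averaged arm effect and would differ for an arm-by-time contrast.

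These objections limit how strongly the point can be put, but they do not remove it. A multilevel model tested at p < 0.05, read in the ordinary way, can miss that level with 12 clusters, and a test that holds it exactly in the balanced case is available from the same data.

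**Conclusion.** The point holds as a conditional one and as an inexpensive improvement, not as an error in what the article states. The degrees of freedom are certain: 12 schools, two arms, 10 df. If the arm coefficient is referred to a normal distribution, the nominal 5% becomes a true rate between about 4% and 10% over ICC 0 to 0.20, with ceilings of 7.8% (REML) and 10.4% (ML). The excess begins at an ICC of roughly 0.01 under ML and 0.02 under REML. The ceilings rest only on normality, balance and an averaged outcome; the values below them also rest on the assumed ICC.

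**What to change.** In Data analysis method, add one sentence making the primary test and its confidence interval valid for 12 clusters. Either of these will do:

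1. **A two-sample t test on the 12 school means, 10 df.** It holds 5.0% at every ICC when schools contribute equal numbers, and it is simple to report. The multilevel model can then be kept as a supporting analysis.
2. **The planned multilevel model by restricted estimation (RIGLS/REML), with the arm coefficient and interval referred to t on 10 df.** This keeps the stated model but is conservative at low ICC: 2.1% at ICC 0 and 3.7% at 0.05.

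State which one is primary, and over which follow-up measure or average, before the data are seen. No new data and no change of design are needed. The cost is the wider interval and the loss of about 9 points of nominal power worked out above; anyone restating the trial's power should use the t-based figure.
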